### Data collection and management

To accurately capture the true severity and clinical heterogeneity of severe acute pancreatitis, comprehensive baseline and dynamic clinical parameters will be systematically recorded in the electronic Case Report Forms (eCRF). These explicitly include: (1) pancreatic enzyme levels over time; (2) daily APACHE II and SOFA scores; (3) the exact degree of extrapancreatic organ involvement and specific organ failures (e.g., respiratory, cardiovascular, and renal impairment); and (4) the requirement and duration of advanced therapeutic interventions, specifically including mechanical respiratory support, hemodynamic support (vasopressors), and CRRT. Recording these decisive clinical variables ensures a rigorous evaluation of the true therapeutic value of HDIVC in the overall care of SAP. Missing data for the primary and secondary outcomes will be addressed using multiple imputation by chained equations (MICE), assuming the data are missing at random. If not, last observation carried forward (LOCF) will be used. Source documents will be maintained for verification. The database will be locked after monitoring and queries resolution for final analysis.

Fecal samples will be collected within 24 h of enrollment (baseline), on treatment Day 7, and on Day 14. Samples will be frozen at −80 °C and shipped to the central laboratory. Total genomic DNA will be extracted, and the V3–V4 hypervariable region of the 16S rRNA gene will be PCR-amplified and sequenced by a certified sequencing service provider.

To minimize inter-center variability, concomitant treatments such as fluid resuscitation and antibiotic use will be guided by the same recommendations for severe acute pancreatitis management (21). Although minor variations reflecting local practice are expected, adherence to a standardized framework will be reinforced through investigator training and regular monitoring. All concomitant therapies will be prospectively recorded, and potential confounding effects will be addressed through statistical adjustment in the final analysis. Center will be included as a random intercept in the primary mixed-effects model to account for clustering of patients within centers.

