### Primary outcome

This study assesses the effect of HDIVC on organ support-free days (OSFD) within the first 14 days in SAP patients. OSFD refers to the number of days a patient does not require circulatory support (vasoactive agents), respiratory support (mechanical ventilation), or renal support (renal replacement therapy). For patients who die within the 14-day observation period, OSFD is assigned a value of 0 day.

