### Statistical methods

The statistical analysis will follow an intention-to-treat (ITT), per-protocol (PP), and safety population approach. All statistical tests will be two-sided, with a *p*-value < 0.05 considered statistically significant. Baseline characteristics will be summarized using descriptive statistics. For quantitative variables, descriptive statistics will include calculations of mean, standard deviation, median, minimum, maximum, and interquartile range (IQR). For categorical variables, descriptive statistics will report frequencies and percentages for each category.

The primary outcome, OSFD within the first 14 days, will be analyzed using a linear mixed-effects model with center included as a random intercept, allowing quantification and adjustment for between-center variability. Sensitivity analyses will treat center as a fixed effect or omit center effects to assess robustness. A treatment-by-center interaction test will be performed to evaluate heterogeneity of treatment effect across sites. The intraclass correlation coefficient (ICC) from the null model will be reported. To control the familywise type I error rate for secondary outcomes, a hierarchical (fixed-sequence) testing procedure is applied. The pre-specified order is: (1) ICU all-cause mortality, (2) SOFA score at Day 7, (3) C-reactive protein at Day 7, (4) APACHE II score at Day 7, followed by all remaining secondary outcomes. Each outcome is formally tested only if all preceding outcomes in the hierarchy reach statistical significance at the two-sided *α* = 0.05 level. Outcomes below the hierarchical chain—including cytokine levels (IL-6, IL-1, IL-10), BISAP score, CTSI score, ICU length of stay, hospitalization costs, and gut microbiota composition—are designated as exploratory. Their *p*-values will be reported descriptively without formal inferential claims.

Bioinformatics processing will use QIIME2 with DADA2 denoising to generate amplicon sequence variants (ASVs), and taxonomic assignment will be performed against the SILVA database. Alpha diversity (Shannon, Chao1 indices) will be compared between groups using Wilcoxon rank-sum tests. Beta diversity (Bray-Curtis, UniFrac distances) will be visualized by principal coordinate analysis (PCoA) and tested by PERMANOVA. Differential abundance analysis will be conducted using LEfSe (LDA > 2.0) and MaAsLin2. Longitudinal changes will be analyzed using linear mixed-effects models if serial samples are available.

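### The fallback from MICE to LOCF has no workable trigger, does not address data missing not at random and is not specified for OSFD, and the rule makes no provision for death in the tested Day-7 outcomes

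*Protocol article*

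**What the plan says.** Under Data collection and management, one rule covers every outcome: "Missing data for the primary and secondary outcomes will be addressed using multiple imputation by chained equations (MICE"). The same sentence states the assumption and the next one gives the alternative: "assuming the data are missing at random. If not, last observation carried forward (LOCF) will be used". No criterion is stated for deciding that MAR fails.

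Under Primary outcome, OSFD is a single count over 14 days: "OSFD refers to the number of days a patient does not require circulatory support (vasoactive agents), respiratory support (mechanical ventilation), or renal support". Death is dealt with there: "For patients who die within the 14-day observation period, OSFD is assigned a value of 0 day".

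Under Statistical methods, the secondary outcomes are tested in a fixed order that begins "1) ICU all-cause mortality, (2) SOFA score at Day 7, (3) C-reactive protein at Day 7, (4) APACHE II score at Day 7", and "Each outcome is formally tested only if all preceding outcomes in the hierarchy reach statistical significance". No death rule is given for the three Day-7 outcomes. The sensitivity analyses named for the primary outcome concern only the handling of center.

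**The concern.** The article does not leave missing data to another document. It fixes a rule, and half of that rule does not work, for three reasons.

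- **Trigger.** MAR and MNAR differ only in how missingness depends on values nobody observed. The observed data therefore cannot settle which holds, and choosing LOCF becomes a judgement made once the data are in hand.
- **Method.** LOCF does not relax MAR. It substitutes another untestable assumption, that nothing changes after the last value, which is implausible in acute organ failure. It also treats filled values as if they had been observed.
- **Application.** OSFD has no earlier OSFD value to carry forward, and the article does not say what would be carried.

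A separate gap concerns death. It is coded into OSFD but not into Day-7 SOFA, CRP or APACHE II, and the missing-data rule covers secondary outcomes without exempting values absent because the patient died. At stake are the credibility of the primary analysis if the fallback were used, and the meaning of any formal Day-7 claim.

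**Working it through.** **1. The plan's own figure.** Inputs from Sample size: difference 2 days, SD 5, two-sided alpha 0.05, power 0.80. n = 2 × [5 × (1.960 + 0.842) / 2]² = 98.1 per group (stated 98). 98 × 1.15 = 112.7, giving 113. 113 / 0.95 = 118.9, giving 119, so N = 238. The figure reproduces. It is used here only to fix the planned missingness at 5%.

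**2. Missing OSFD values.** 0.05 × 238 = 11.9, about 12 patients; 0.05 × 119 = 5.95, about 6 per arm. Deaths within 14 days are not among them, because they are set to 0.

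**3. How far missing values can move the primary result.** Shift in an arm's mean = proportion missing × change in the missing values.

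| Change among the missing | Shift |
|---|---|
| 14 days, one arm (extreme bound) | 0.05 × 14 = 0.7 day |
| 14 days, arms in opposite directions | 2 × 0.7 = 1.4 days |
| 1 day, one arm | 0.05 day |
| 2 days, one arm | 0.10 day |
| 4 days, one arm | 0.20 day |
| 7 days, one arm | 0.35 day |

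The target difference is 2 days. The first two rows bound any imputation method; they do not measure LOCF in particular. On precision, counting 119 values per arm as observed when 113 are multiplies the standard error by √(113/119) = 0.974, about 2.6% too narrow from the count alone.

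**4. What LOCF could mean for OSFD.** The article records the duration of ventilation, vasopressors and CRRT, so daily support status could be carried forward. A patient last seen on Day k then receives either 0 or 14 − k further support-free days, depending only on status that day:

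- Day 3: 0 or 11
- Day 7: 0 or 7
- Day 10: 0 or 4

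**5. Patients without a Day-7 score because of death.** The Introduction gives background mortality of 13 to 35%. The share of deaths occurring by Day 7 is not in the document; take 25 to 75% as an assumption.

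- Lowest: 238 × 0.13 × 0.25 = 7.7, about 8
- Highest: 238 × 0.35 × 0.75 = 62.5, about 62
- At 50%: 238 × 0.13 × 0.5 = 15.5 to 238 × 0.35 × 0.5 = 41.7, about 15 to 42

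Over most of this range the number exceeds the 12 planned dropouts.

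**6. Why the handling of death matters (all inputs assumed).** Suppose 15% versus 9% are dead by Day 7 and survivors in both arms average SOFA 6. The arm difference is (0.15 − 0.09) × (fill − 6):

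- filled at the survivor mean: 0
- filled with a last score of 12: 0.06 × 6 = 0.36
- death scored 24: 0.06 × 18 = 1.08

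A simulation lets sicker patients die more often. Baseline SOFA has mean 9 and SD 3, the SOFA course is identical in both arms, and deaths by Day 7 are 15% control versus 8% HDIVC. HDIVC minus control is then +0.23 in survivors only, −0.11 with LOCF, 0.00 with model imputation and −1.02 with death scored 24. Sign and size depend on the convention chosen.

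**The case against.** The main method, MICE under MAR, is standard and is not in dispute. The fallback is contingent, planned dropout is 5%, and death is already defined for the primary outcome. All of this stands, and it limits the severity.

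Four stronger readings are tempting, and the document does not support them.

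- **That dead patients' Day-7 scores will be filled in.** The text never says that post-death scores count as missing. It only fails to exempt them, and an analysis plan not shown may do so.
- **That LOCF is impossible for OSFD.** It could be applied to daily support status. It is unspecified, and the result would be arbitrary, but it is not undefined.
- **That the arm with more deaths would look better on SOFA because of this rule.** The arithmetic example shows only a difference shrunk relative to scoring death as 24. The value of 0 assumes imputation at the survivor mean, whereas SOFA is to be recorded daily and MICE could use the scores before death.
- **That the primary result could be off by 0.7 day because of LOCF.** That figure is an extreme bound for any method.

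Two mitigations carry some weight. Day-7 SOFA is formally tested only after a significant ICU mortality result, so a SOFA claim could not stand alone. But a significant mortality difference is exactly when deaths by Day 7 are likely to be unbalanced, and the two-sided test opens the gate in either direction. Second, Randomization and blinding withholds which group is which until the analysis is complete. That reduces, but does not remove, the concern about a choice made after the data are seen: the split into two groups is already visible, and comparing plasma vitamin C, a listed secondary outcome, could reveal the labels.

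The absence of a missing-data sensitivity analysis from a condensed article is not itself a fault. The fault is that the article names LOCF for that role.

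**Conclusion.** The point holds against the LOCF fallback, not against MICE under MAR. As written, the fallback has no usable trigger, does not answer the problem it is invoked for, and has no stated meaning for OSFD. The Day-7 outcomes need a stated treatment of death because, read literally, the rule would impute them after death.

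The likely effect on the primary outcome is modest if dropout stays at the planned 5%: 0.05 to 0.35 day on the difference for shifts of 1 to 7 days among one arm's missing patients, with the 0.7-day bound as the extreme for one arm. The Day-7 gap could involve more patients, but its size rests on an assumed timing of death, and the SOFA illustrations rest wholly on assumed inputs. This should be fixed; it does not make the planned primary analysis invalid.

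**What to change.** - Delete the LOCF fallback.
- Keep MICE under MAR as the main analysis, using baseline severity and the organ-support days already observed, with death within 14 days still scored 0 for OSFD.
- Replace LOCF with a prespecified delta-adjusted or tipping-point sensitivity analysis that is always reported, so that no decision about MAR is needed.
- State that Day-7 SOFA, CRP and APACHE II are not imputed after death, and prespecify one death strategy for each. A worst-rank composite and a survivor estimand are both accepted, and the choice is the sponsor's. A composite moves the result to a rank scale and repeats some of the mortality information, which is most debatable for CRP. A survivor comparison is open to selection when deaths differ between arms.

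The cost is wording in the protocol and analysis plan and a little more analysis, with no new data and no change in N. The change should be made before any results by group are seen, including those at the interim analysis.

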### Statistical methods

The statistical analysis will follow an intention-to-treat (ITT), per-protocol (PP), and safety population approach. All statistical tests will be two-sided, with a *p*-value < 0.05 considered statistically significant. Baseline characteristics will be summarized using descriptive statistics. For quantitative variables, descriptive statistics will include calculations of mean, standard deviation, median, minimum, maximum, and interquartile range (IQR). For categorical variables, descriptive statistics will report frequencies and percentages for each category.

The primary outcome, OSFD within the first 14 days, will be analyzed using a linear mixed-effects model with center included as a random intercept, allowing quantification and adjustment for between-center variability. Sensitivity analyses will treat center as a fixed effect or omit center effects to assess robustness. A treatment-by-center interaction test will be performed to evaluate heterogeneity of treatment effect across sites. The intraclass correlation coefficient (ICC) from the null model will be reported. To control the familywise type I error rate for secondary outcomes, a hierarchical (fixed-sequence) testing procedure is applied. The pre-specified order is: (1) ICU all-cause mortality, (2) SOFA score at Day 7, (3) C-reactive protein at Day 7, (4) APACHE II score at Day 7, followed by all remaining secondary outcomes. Each outcome is formally tested only if all preceding outcomes in the hierarchy reach statistical significance at the two-sided *α* = 0.05 level. Outcomes below the hierarchical chain—including cytokine levels (IL-6, IL-1, IL-10), BISAP score, CTSI score, ICU length of stay, hospitalization costs, and gut microbiota composition—are designated as exploratory. Their *p*-values will be reported descriptively without formal inferential claims.

Bioinformatics processing will use QIIME2 with DADA2 denoising to generate amplicon sequence variants (ASVs), and taxonomic assignment will be performed against the SILVA database. Alpha diversity (Shannon, Chao1 indices) will be compared between groups using Wilcoxon rank-sum tests. Beta diversity (Bray-Curtis, UniFrac distances) will be visualized by principal coordinate analysis (PCoA) and tested by PERMANOVA. Differential abundance analysis will be conducted using LEfSe (LDA > 2.0) and MaAsLin2. Longitudinal changes will be analyzed using linear mixed-effects models if serial samples are available.

Prespecified subgroup analyses will examine treatment effects by disease severity and baseline characteristics using interaction tests. All analyses will be performed using SAS 9.4, adhering to CONSORT guidelines.

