### Randomization and blinding

Participants will be strictly enrolled based on predefined eligibility criteria. Stratified block randomization will be employed by each research center. Patients will be allocated to either the HDIVC group or control group, with allocation concealment maintained throughout. Randomization numbers will be generated by statisticians using SAS 9.4 software, employing block randomization within each stratum to ensure balanced group assignment. Expansion of the sample size may be considered if necessary.

Stratification is performed at three levels: (1) participating center (8 centers), and (2) etiology, categorized as biliary, hypertriglyceridemic, alcoholic or other. Due to our rigorous inclusion criteria, all enrolled patients are diagnosed with SAP. We will not proceed stratification by disease severity. The randomization sequence is generated independently for each stratum combination (8 × 4 = 32 strata) by an independent statistician using SAS 9.4, employing variable block sizes of 4 and 6 (randomly alternated) to ensure allocation concealment and balance within each stratum.

To ensure blinding, study medications—either 50 mL vitamin C solution or matching placebo (0.9% normal saline)—will be prepared in identical, opaque, light-proof containers by UDPN according to the randomization list. Both groups will receive equal volumes (50 mL) via identical administration protocols using the standardized micropump (2 g/h). Crucially, the administration through a central vein minimizes potential sensory cues (such as infusion site irritation) that could arise from pH differences, thereby maintaining the blind for participants, clinical staff, and data analysts. All centers will follow this standardized protocol after thorough training and the study medicine is provided by one center to avoid bias.

The data management and analysis will implement a two-stage unblinding process. After all data have been locked following blinded data verification, the group assignments for each participant will be disclosed for statistical analysis. When the statistical analysis completes, the specific group assignments (intervention group or control group) will be disclosed to assess the study outcomes.

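### The primary model adjusts for centre only, leaving out the etiology stratification factor and the baseline severity data already collected

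*Protocol article*

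**What the plan says.** The primary model is described twice in the protocol article. Under Statistical methods, OSFD "will be analyzed using a linear mixed-effects model with center included as a random intercept". Under Data collection and management: "Center will be included as a random intercept in the primary mixed-effects model to account for clustering of patients within centers". Neither sentence names another covariate. The named robustness checks also vary centre alone: "Sensitivity analyses will treat center as a fixed effect or omit center effects to assess robustness". The treatment-by-centre test and the intraclass correlation from the null model likewise concern centre only.

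The design uses more than centre. Under Randomization and blinding, the second stratification factor is "etiology, categorized as biliary, hypertriglyceridemic, alcoholic or other", and "The randomization sequence is generated independently for each stratum combination (8 × 4 = 32 strata". Etiology does not appear in the analysis text. On severity the same section says: "We will not proceed stratification by disease severity".

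Table 1 schedules SOFA, APACHE II, mechanical ventilation, vasoactive drugs and CRRT on Day 0. Baseline data are otherwise used for descriptive summaries and for subgroup interaction tests. Under Intervention, Data collection and management, and Monitoring, the article mentions adjustment for CRRT parameters and concomitant therapies, but it neither specifies this nor ties it to the primary model.

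**The concern.** Two separate things are lost.

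- **Etiology.** Stratified blocks balance the arms within etiology, so the true sampling variance of the treatment difference is smaller than under simple randomisation. A model without etiology leaves the between-etiology variation in the residual. Its standard error is then too large, and the test is conservative to the extent that etiology predicts outcome.
- **Baseline severity.** OSFD counts days without vasoactive drugs, mechanical ventilation or renal replacement. Whether a patient is already receiving these on Day 0 is plausibly among the strongest predictors of the outcome. Because severity is not stratified, a chance imbalance in baseline support passes directly into the unadjusted estimate.

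The adjustment the article does promise is no substitute. CRRT parameters and concomitant therapies arise largely after randomisation, and renal replacement is itself a component of OSFD. Conditioning on it could remove part of the treatment effect.

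At stake are wider intervals than necessary and some avoidable loss of power. Type I error is not inflated.

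**Working it through.** **Inputs from the Sample size section:** difference 2 days, SD 5, two-sided alpha 0.05, power 0.80; 98 per group, raised by 15% to 113, then to 119 for 5% dropout. **Assumed:** R², the share of OSFD variance explained by the added baseline covariates. The documents do not give it, so it is varied.

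**1. The plan's own figures.** n = 2 × [5 × (1.960 + 0.842) / 2]² = 98.1 per group (stated as 98). Then 98 × 1.15 = 112.7, so 113; and 113 / 0.95 = 118.9, so 119 per group and 238 in total. These reproduce.

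**2. Precision with adjustment.** Residual SD = 5 × √(1 − R²); SE = residual SD × √(2/113); power = Φ(2/SE − 1.96); equivalent unadjusted n = 113/(1 − R²).

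| R² (assumed) | Residual SD | SE (days) | Power, 113 per arm | Equivalent n per arm |
|---|---|---|---|---|
| 0 | 5.000 | 0.665 | 85.2% | 113 |
| 0.05 | 4.873 | 0.648 | 87.0% | 119 |
| 0.10 | 4.743 | 0.631 | 88.7% | 126 |
| 0.20 | 4.472 | 0.595 | 92.0% | 141 |
| 0.30 | 4.183 | 0.557 | 94.9% | 161 |

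Using the t distribution, power at R² of 0, 0.10, 0.20 and 0.30 is 84.9%, 88.4%, 91.7% and 94.7%. The SE falls by about 5% at R² = 0.10 and 16% at R² = 0.30.

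The 15% uplift is meant to pay for non-normality. If it is wholly used up, the relevant size is 98 per arm, and power at the same four R² values is 80.0%, 83.9%, 87.9% and 91.7%. The gain is similar or slightly larger.

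**3. Omitting etiology after stratifying on it.** A simulation used 226 evaluable patients, 8 centres, 4 etiologies (assumed shares 35%, 35%, 10%, 20%), blocks of 4 and 6 within the 32 strata, a normal outcome with SD 5, and centre as a fixed effect. There were 4,000 null runs and 2,000 runs with a 2-day effect.

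| Etiology / severity share of variance | Model | Type I error | Power |
|---|---|---|---|
| 10% / 20% | centre only | 3.7% | 85.5% |
| | + etiology | 4.7% | 87.7% |
| | + etiology + severity | 4.7% | 94.6% |
| 5% / 20% | centre only | 4.7% | 85.1% |
| | + etiology | 5.3% | 86.6% |
| | + etiology + severity | 4.9% | 93.4% |

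The Monte Carlo error of a 5% rate over 4,000 runs is √(0.05 × 0.95/4000) = 0.34 percentage points. The 3.7% is therefore real conservatism (a repeat gave about 3.9%), whereas the 4.7% is indistinguishable from nominal.

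**4. Chance imbalance.** Suppose half of patients have a given support at baseline (assumed). The SE of the difference in proportions is √(2 × 0.25/113) = 0.0665. An imbalance of 10 points or more is 1.50 SE, with a probability of about 13%. If that support shifts OSFD by 4 days (assumed), a 10-point imbalance moves the estimate by 0.10 × 4 = 0.4 days, one fifth of the 2-day target.

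**The case against.** The strongest objection is that silence is not exclusion. This is a condensed article, the statistical analysis plan is not shown, and covariate lists often sit there. That would carry weight if the article had left the model open. It does not: it states the model twice, lists the sensitivity analyses, and treats centre alone throughout. A later plan with more covariates would be changing what is published here.

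The other points stand in part:

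- **No validity error.** Correct. In a linear model under randomisation, omitting baseline covariates neither biases the effect nor inflates type I error, and the unadjusted SE already allows for chance imbalance. The trial was sized without covariates.
- **The size is assumed.** Correct. All patients have persistent organ failure, which narrows the severity range and could keep R² low. The simulation used a normal outcome, not a 0 to 14 count with deaths set to 0. Etiology alone contributes little.
- **The promised adjustment might include baseline CRRT**, since Table 1 records CRRT on Day 0. Possible, but it is unspecified, and it would cover neither etiology nor the severity scores.
- **The exact covariate set is partly a choice.** SOFA overlaps with the support indicators, and the article states no model for the Day 7 secondary outcomes. This affects the details of the remedy, not the case for one.

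**Conclusion.** The point holds. As published, the primary analysis omits one of the two randomisation factors and uses no baseline severity measure, although both are available on Day 0. The cost is efficiency. If the covariates explain 10% to 30% of OSFD variance, adjustment adds about 3.5 to 10 percentage points of power, equivalent to 13 to 48 more patients per arm. At R² of 0.05 or less, the gain is below 2 points. Most of the gain would come from baseline severity. Etiology belongs in the model mainly because the analysis should follow the randomisation; its omission makes the test visibly conservative only if etiology explains something like 10% of variance. These figures rest on the protocol's 2 days and SD 5, on the assumed R², and on a normal approximation for a bounded outcome. The planned 238 is unaffected. This is an improvement that should be made; it does not invalidate the trial.

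**What to change.** Fix the primary model as OSFD on treatment arm, etiology (four levels), baseline SOFA and organ support at randomisation (ventilation, vasoactive drugs and renal replacement, each yes/no), with the random intercept for centre retained. If the overlap between SOFA and the support indicators is a worry, choose a smaller set, but name it in advance. Keep the centre-only model as a sensitivity analysis. State that therapies begun after randomisation, including CRRT parameters, do not enter the primary model. For Day 7 SOFA, C-reactive protein and APACHE II, include the baseline value of the same measure.

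The cost is wording in the protocol and statistical analysis plan, plus a rule for missing baseline values. The model gains seven fixed-effect parameters (3 + 1 + 3), which about 226 evaluable patients can support. No new data collection is needed. Because the lead centre has already recruited 34 patients, the change should be dated and justified before the interim analysis or any other unblinded look.

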## Method and analysis

### Study design

This prospective, randomized, double-blind, multicenter trial will investigate whether early intravenous HDIVC reduces OSFD within the first 14 days in SAP patients. We will enroll 238 participants (119 per group) from eight hospitals across China, with block randomization allocating patients to either HDIVC or control groups. Serial assessments of organ function, disease severity scores, and mortality will be evaluated at predefined time points before and after treatment to determine therapeutic efficacy. The evaluation and examination will be continued from randomization to 180 days or death. Figure 1 shows the flow chart of the study. This study protocol is written according to the Standard Protocol Items for Randomization Trials (SPIRIT) statement (18).

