### Secondary outcome

The secondary outcomes are: (1) ICU all-cause mortality, defined as death from any cause from randomization to ICU discharge or transfer. (2) Early SAP inflammatory markers, including C-reactive protein and cytokines IL-6, IL-1, and IL-10. (3) Organ function scores, including SOFA and modified Marshall scores. (4) Fluid retention. (5) Disease severity scores, including APACHE II and BISAP scores. (6) Pancreatic necrosis measured by CTSI scores. (7) Other prognostic indicators including the incidence of infected pancreatic necrosis, ICU length of stay, and hospitalization costs. (8) Plasma vitamin C concentrations before and after treatment. (9) Adverse events related to vitamin C. (10) Gut microbiota composition.

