### Sample size

The sample size calculation is based on the primary outcome of OSFD within the first 14 days. Assuming the HDIVC group would gain 2 additional OSFD days compared to the control group (SD 5 days), with a two-sided *α* of 0.05 and power of 0.80, the initial calculation using the formula for two independent sample means required 98 patients per group. To account for non-normal distribution of OSFD, the Pitman asymptotic relative efficiency correction expanded the sample by 15% to 113 per group. Allowing for a 5% dropout rate, the final sample is 238 patients (119 per group). The study plans to recruit 10 patients per month over 24 months. Ethical approval has been gained in participating centers. Centralized online training has been completed to ensure protocol adherence. As of May 30, 2026, the lead center has recruited 34 patients. Participating centers are being activated, which will increase recruitment capacity.

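### The secondary testing chain does not depend on the primary outcome, contradicts itself on where it ends, and opens with a mortality outcome that has no fixed time window

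*Protocol article*

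**What the plan says.** Four places in the protocol article bear on this.

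- **Scope and gate (Statistical methods).** "To control the familywise type I error rate for secondary outcomes, a hierarchical (fixed-sequence) testing procedure is applied". The order is ICU all-cause mortality, SOFA at Day 7, C-reactive protein at Day 7, APACHE II at Day 7. Each test needs every earlier member of the hierarchy to be significant at two-sided 0.05. OSFD is not a member.
- **End of the chain (Statistical methods).** The four named tests are "followed by all remaining secondary outcomes". Shortly after, outcomes below the chain (cytokines, BISAP, CTSI, ICU stay, costs, gut microbiota) "are designated as exploratory", with p-values reported only descriptively.
- **Mortality window (Secondary outcome).** ICU mortality is "defined as death from any cause from randomization to ICU discharge or transfer". Study design says: "The evaluation and examination will be continued from randomization to 180 days or death". Table 1 records death at Day 180.
- **Sizing (Sample size).** "The sample size calculation is based on the primary outcome of OSFD within the first 14 days". No power statement is given for mortality.

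**The concern.** The article fixes the order, the gate and the alpha itself, so these are statements to be judged and not details left to an analysis plan.

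Three things follow from the wording. First, if OSFD misses, nothing stops the team from testing ICU mortality at 0.05 and reporting it as a confirmatory result; the primary and the head of the chain then each carry a full 5%. Second, the status of a good part of the secondary list depends on which of two sentences is followed, and that choice could be made after the data are seen. Third, the outcome that opens the chain has a window that varies by patient: someone transferred out of the ICU who then dies is counted as a survivor, although the trial goes on following that patient.

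**Working it through.** **1. The plan's own sample size, to fix the number per arm**

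Inputs from Sample size: difference 2 days, SD 5 days, two-sided 0.05, power 0.80.

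- n per group = 2 × (1.960 + 0.842)² × 5² / 2² = 98.1. This is 98 as stated, or 99 if rounded up; 98 gives power 0.7996.
- 98 × 1.15 = 112.7, so 113. Then 113 / 0.95 = 118.9, so 119 per group and 238 in total.

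The stated figure reproduces. It is a calculation for OSFD only.

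**2. Error across the primary and the first secondary**

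Both are tested at overall two-sided 0.05, with no gate between them. Under no effect on either, the chance of at least one false claim is as follows.

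- Independent tests: 1 − 0.95² = 0.0975.
- Upper bound: 0.05 + 0.05 = 0.10.
- Correlated tests, by simulation of two standard normal statistics (2 million draws, either |Z| above 1.96):

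| Assumed correlation | At least one false claim | If gated on the primary |
|---|---|---|
| 0 | 0.098 | 0.050 |
| 0.3 | 0.095 | 0.050 |
| 0.5 | 0.091 | 0.050 |
| 0.7 | 0.083 | 0.050 |

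The correlation is not zero, because OSFD is set to 0 for deaths within 14 days. Its size is not given, so the range is an assumption.

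**3. Where each secondary outcome stands**

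| Status in Statistical methods | Outcomes from the Secondary outcome list |
|---|---|
| Named and ordered in the chain | ICU mortality, SOFA, C-reactive protein, APACHE II |
| In the chain by one sentence, exploratory by another | IL-6, IL-1, IL-10, BISAP, CTSI, ICU stay, costs, gut microbiota |
| Named in neither list | Fluid retention, modified Marshall score, infected pancreatic necrosis (also plasma vitamin C and adverse events) |

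A fixed sequence cannot run through a group that has no order, so the first sentence cannot be carried out even if it is the one intended.

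**4. Power of the first link (a caution)**

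The article gives no ICU mortality assumption. The only range it offers is background mortality of 13 to 35% (Introduction), used here as an assumed control rate. The risk ratios are also assumed. With d = p₁ − p₂ and p̄ the mean of the two rates:

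Power = Φ{[d − 1.96 √(2p̄(1−p̄)/n)] / √[(p₁(1−p₁) + p₂(1−p₂))/n]}

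Example, n = 119, 30% against 22.5%: (0.075 − 1.96 × 0.0570) / 0.0568 = −0.65, so power is 0.26.

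| Control rate | Power, RR 0.75 | Power, RR 0.5 |
|---|---|---|
| 13% | 12% | 39% |
| 20% | 17% | 58% |
| 25% | 21% | 70% |
| 30% | 26% | 80% |
| 35% | 31% | 87% |

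At a 30% control rate, 80% power needs a fall to 14.9%.

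**The case against.** The plan claims error control for the secondary outcomes only, and a fixed sequence at 0.05 delivers that within the four ordered tests. Handling one primary and a secondary family separately is a recognised choice. This stands: the procedure does not fail at its stated scope. What remains is that the text permits a confirmatory secondary claim after a failed primary.

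A reader might infer that the primary and mortality are two independent routes to a positive result. They are not, because early deaths set OSFD to 0. The 9.75% is the independence figure and not this trial's rate.

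A reader might also infer that the later endpoints cannot be tested. With a risk ratio of 0.75 the chain would stop at step 1 in 69 to 88% of trials (100% minus 31% and minus 12%), but that effect is nowhere in the article, and a halving from 30 to 35% gives 80 to 87% power. Placing mortality first by clinical importance is legitimate, and stopping there is how a fixed sequence works. Moving SOFA Day 7 to the front is no clear gain, since it cannot be observed in patients who die before Day 7.

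On the end of the chain, the exploratory list is introduced as non-exhaustive, so unnamed outcomes may be meant to fall there. That is a fair reading, but it does not remove the clash with the sentence that puts all remaining secondaries in the chain.

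On the window, ICU mortality is clearly defined and its variable length is inherent in it. That it would differ by arm is not shown. Counting a death after transfer as survival does follow from the definition.

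**Conclusion.** The point holds in limited form, and the section is wrong as written.

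- **Gate.** A formal ICU mortality claim is allowed after OSFD fails. The false-claim rate over these two tests is about 8 to 10% in place of 5%. The exact value depends on an unknown correlation; no correlation from 0 to 0.7 brings it below 8.3%.
- **End of the chain.** The two sentences contradict each other. This needs no outside assumption.
- **Window.** The first link ignores deaths after ICU discharge or transfer that the trial's own follow-up should capture.
- **Power.** This is a caution only. The 12 to 31% and 39 to 87% rest on background mortality used for ICU mortality and on assumed risk ratios. They support saying that the chain may often stop at step 1, and no more.

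**What to change.** 1. State that the secondary chain opens only if OSFD meets its significance boundary, including the boundary that applies under the O'Brien–Fleming interim plan.
2. End the chain at APACHE II Day 7. Delete the clause that adds the remaining secondaries, and list every other secondary outcome by name as exploratory, including fluid retention, modified Marshall score and infected pancreatic necrosis.
3. Use all-cause mortality at a fixed time in the chain, for example Day 28 with Day 180 as supportive, and keep ICU mortality as descriptive. Follow-up already runs to Day 180; the date of death must be recorded, since Table 1 marks death only at the Day 180 column.
4. The place of mortality in the order is the sponsor's choice. Keeping it first needs only a sentence acknowledging the limited power. Putting SOFA Day 7 first is not required and would need a rule for deaths before Day 7.

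The cost is a wording amendment, made while the lead center reports 34 of 238 patients recruited. It adds no patients or visits. The downside is that no formal secondary claim, mortality included, can be made if the primary fails.
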